### Study design

This multinational and multicenter longitudinal study has a quasi-experimental randomized controlled trial design. The study consists of one intervention group (IG) and one waiting list control group. The intervention group will first address physical activity then fruit and vegetable consumption. The waiting list control group will get access to the intervention after the study condition has finished the intervention (T3). The waiting list control group has to complete the baseline questionnaire (T1) at the same time as the intervention group and will have access to the intervention only after their second measurement. In total, six data collection time points are planned where T0 is intended for the collection of contact information only. Baseline measurement will take place at T1 before the intervention starts, followed by a measurement (T2) after completion of the intervention. Further follow-up measurements are planned to take place after four weeks (T3), after six months (T4) and after 12 months (T5) (see Table 1).

**Table 1 T1:** Design of measurement points

**Time point**	**Measurement**
T0	Patients within cardiac rehabilitation will be asked if they are interested in participation of an aftercare program. Contact data will be collected

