	**End of the intervention period**
	**Waiting list control group starts intervention**
T3	4 week follow-up measurement
T4	6 month follow-up measurement
T5	12 month follow-up measurements

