### Power analysis

The power analysis was based on the assumption that the intervention will result in a small improvement of effect to improve fruit and vegetable consumption and in a small to medium effect to improve physical activity for the study conditions [38]. The calculation was based on an effect size of 0.3, with a power (1-β) of 0.8 and alpha of 0.05.

No cluster effect is expected due to the fact that the randomization of the participants is independent of the place of recruitment. Further, it is necessary to take interaction effects into account between the intervention and the control group, and between Germany and the Netherlands.

Therefore, to be able to detect a small to medium effect, 263 people have to participate in every group in each country. This means that the required total sample size will need to consist of 1052 participants, not adjusted for potential drop out during the intervention.

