### Randomization

During the rehabilitation period, patients will be recruited within the rehabilitation center by their therapists. These therapists will first inform the person undergoing rehabilitation about the study and hand out study information. Participants will log in on the project website and have to give online informed consent. Randomization will be done by the computer software *TailorBuilder*, which is developed for internet based tailored interventions. Participants will be randomly allocated to the study group or to the waiting list control group. The waiting list control group will get access to the intervention after eight weeks (see Table 1).

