### Statistical analysis

Descriptive statistics will be used to describe baseline characteristics of the study. We will assess whether there are significant differences between the intervention group in comparison with the control group according to physical activity and nutrition by means of linear regression analysis in PASW (SPSS). The pre-test and post-test measurements of the control group will be compared with the measurements of the intervention and controle group with regard to the target behaviours.

To be able to assess the impact of the intervention on the performance of physical activity and fruit and vegetable consumption, we intend to perform several analyses of covariance (ANCOVA) after four weeks (T3) and six months (T4), controlling for the baseline performance. Multivariate regression analysis will be used to determine possible confounding or modification effects. Regression analysis will allow us to identify the percentage of variability of the dependent variable that is explained by the determinants used. In order to detect differences between the study condition and the control group, effect sizes will be calculated for each study group separately [78].

Subgroup analyses will be performed to determine if the benefit of the intervention depends between groups like nationality or socioeconomic status [79]. Further, dose–response-analyses will be conducted with logistic regression to see if the intervention effect depended on the time spent on the webpage.

Baseline characteristics of participants who dropped out will be compared with participants who finished the intervention to examine whether drop out is at random or determined by specific characteristics.

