## Discussion

The results of this study are important for the future development of online-based rehabilitation aftercare programs for cardiovascular patients and the development of online interventions in general. Although there is no doubt about the positive effect of adequate physical activity and fruit and vegetable consumption for people undergoing rehabilitation [8,11,13,17,22,80], many patients fail to maintain lifestyle changes [26-28]. To transfer the rehabilitation results into the daily life and to overcome unhealthy habits, effective rehabilitation aftercare is necessary.

Given the benefit of tailored health behavior change interventions, there is still a need for further research. It is important to develop guidelines for interventions which are effective in different countries with different rehabilitation systems. In order to make a positive contribution, an international implementation and evaluation of this study will be done within Germany and the Netherlands.

It will be assessed to what extent the health status, quality of life and return to the labor market can be realized among the participants. Our hypothesis is that participants in the intervention group will increase their level of physical activity, fruit and vegetable consumption and are able to maintain these behaviors over a longer period of time compared to the control group.

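### The 12-month measurement (T5) is scheduled but assigned to no stated effect analysis, and the end-of-intervention measurement (T2) is also missing from the named ANCOVA time points

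*Protocol article*

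**What the plan says.** The Study design section places baseline at T1 and a measurement at the end of the eight-week programme at T2. It continues: "Further follow-up measurements are planned to take place after four weeks (T3), after six months (T4) and after 12 months (T5"). Table 1 repeats the last of these as "12 month follow-up measurements".

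The Statistical analysis section states how impact on the two target behaviours will be assessed: "several analyses of covariance (ANCOVA) after four weeks (T3) and six months (T4), controlling for the baseline performance". T5 and T2 are not in that list. The same section also plans a linear regression comparing the groups on physical activity and nutrition, multivariate regression, effect sizes, subgroup analyses and a dose-response analysis, all without a time point. It plans a pre-test and post-test comparison as well: "The pre-test and post-test measurements of the control group will be compared with the measurements of the intervention and controle group". That comparison does not mention the 12-month follow-up.

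The Discussion gives the hypothesis that intervention participants will improve both behaviours and "are able to maintain these behaviors over a longer period of time compared to the control group".

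On control access, the Randomization section says: "The waiting list control group will get access to the intervention after eight weeks". Table 1 agrees, with the waiting list group starting the programme between T2 and T3.

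**The concern.** Design, hypothesis and analysis do not agree on which measurements carry the assessment of effect. The design follows participants to 12 months, and the hypothesis is about maintenance. The analysis paragraph names its time points by label and leaves out the last one, which is the furthest from the programme.

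Two things are at stake. First, participants are asked for a 12-month measurement with no stated use in assessing effect. Second, if the assignment is made only once T3 and T4 results are known, whether and how T5 is reported becomes a choice open to influence from the data. Nothing shows that this will happen, but the article does not close the possibility.

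The absence of T2 matters for a different reason. Under Table 1 and the Randomization section, T2 is the only post-baseline measurement taken before the control group can use the programme, so it gives the one comparison with controls who have not yet had access.

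**Working it through.** No figure in the plan bears on this point. The check sets the measurement schedule against the analyses.

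**1. Schedule against the ANCOVA list** (Study design, Table 1, Randomization, Statistical analysis)

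| Measurement | Timing | Control group's access (Table 1, Randomization) | Named in the ANCOVA? |
|---|---|---|---|
| T1 | Baseline | None | As covariate |
| T2 | End of programme, 8 weeks | Not yet | No |
| T3 | 4-week follow-up | Has access | Yes |
| T4 | 6-month follow-up | Has access | Yes |
| T5 | 12-month follow-up | Has access | No |

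T0 collects contact details only and is left out.

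**2. Count.** There are four post-baseline measurements (T2 to T5). Two are named (T3, T4) and two are not (T2, T5): 2/4 = 50%. T5 alone is 1/4 = 25%. The gap between the last named time point and the last scheduled one is 12 − 6 = 6 months.

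**3. Can another stated analysis hold T5?**
- Group comparison by linear regression: no time point.
- Pre-test and post-test comparison: the 12-month follow-up is not mentioned. A natural reading of post-test is T2, but the text does not say so.
- Multivariate regression, effect sizes, subgroup and dose-response analyses: no time point.
- Comparison of drop-outs with completers: uses baseline characteristics and is not an effect analysis.

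None of these is stated to use T5, and none excludes it. Across the article, T5 appears only in the Study design section and Table 1.

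**4. What T5 could estimate.** Controls start after eight weeks, so by T5 both groups have been offered the programme. The T5 contrast is immediate against delayed access. The same holds at T4 and, under Table 1, at T3.

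One sentence in Study design is less clear: it ties control access to T3, while a later sentence in that section puts access after the second measurement. If access came only at T3, the T3 contrast could also precede it. T4 and T5 would be unaffected.

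**5. Number of participants.** The Power analysis section requires 263 × 4 = 1052 participants and says that this is not adjusted for drop-out. So 1052 is a ceiling for T5 data, not an expected number.

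**The case against.** The strongest reply is that this is a condensed article. Assigning each visit to a model is commonly left to a full protocol or analysis plan, neither of which is shown, and naming two ANCOVA time points does not contradict collecting a third. This carries some weight, and the point would fall if the article had been silent on time points. It is not silent: it lists the ANCOVA time points by label and omits the last scheduled one. That is a mismatch in what is stated, and a reader cannot tell whether it is deliberate.

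A reader might infer more: that effect reporting ends at six months, that T5 will go untested, or that this omission is what prevents the trial from showing durability. The documents do not support these readings.
- The Statistical analysis section does not restrict the effect analysis to T3 and T4, and several of its analyses could take T5.
- The hypothesis sets no 12-month horizon, and a six-month result after an eight-week programme can bear on it.
- Durability against an untreated control is out of reach at T5 because of the waiting-list design, whether or not T5 is analysed.

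The waiting-list design does not explain leaving out T5 alone, however. It affects T4 equally, and T4 is analysed.

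**Conclusion.** The point holds in limited form. T5 is scheduled and has no stated effect analysis, although the hypothesis concerns maintenance. T2, the contrast before control access, is also missing from the ANCOVA list. Half of the post-baseline measurements, two of four, are therefore not named in the analysis that assesses impact. T5 is unassigned rather than excluded.

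This does not invalidate the T3 and T4 analyses, and no bias or loss of power is claimed. The consequence is an open choice about the six months between T4 and T5, and about the cleanest between-group contrast at T2. It should be settled before outcome data are seen.

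The conclusion assumes that Table 1 and the Randomization section give the intended time of control access, and that no document outside the article already assigns T5 and T2. If one does, the remedy is to bring the article into line with it.

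**What to change.** In the Statistical analysis section:
- Add T5 to the baseline-adjusted analysis of both behaviours, as a secondary contrast labelled immediate versus delayed access.
- Name T2 as the contrast before control access.
- Either form of model will do: an ANCOVA at each measurement, or one repeated-measures model over T2 to T5 with baseline adjustment. The choice is one of preference.

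If T5 is not to be analysed for effect, say so and limit the maintenance hypothesis in the Discussion to six months.

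The cost is a few lines of wording and the extra model time points. All the measurements are already planned, so no new data are needed. The small downside is that additional secondary contrasts must be reported.

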### Main study outcomes

The primary study parameter of this study is to analyze the effectiveness of a rehabilitation aftercare program with regard to the level of physical activity and fruit and vegetable intake. The effect of the program will be compared between the intervention group and the control group as well as between the different countries. Secondary study parameters that will be investigated are self-efficacy, outcome expectations, habit, compensatory cognitions, social support, action and coping planning, intention to change, duration absence from work, quality of life and wellbeing. The other study parameters which will be considered are demographic variables, socioeconomic status, stage, age, gender, depression, and health status.

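### The effect size meant to show a difference between the arms is to be computed one arm at a time, so it does not estimate that difference

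*Protocol article*

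**What the plan says.** All of the relevant analysis text is in the Statistical analysis section of the protocol article.

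- **Effect size:** "In order to detect differences between the study condition and the control group, effect sizes will be calculated for each study group separately". The method is given by a citation, and the article does not define the measure.
- **Pre-test and post-test:** "The pre-test and post-test measurements of the control group will be compared with the measurements of the intervention and controle group", with the two target behaviours as the subject of the comparison.
- **Between-arm tests:** the section plans to look for "significant differences between the intervention group in comparison with the control group according to physical activity and nutrition by means of linear regression analysis". To assess the impact of the intervention it plans "several analyses of covariance (ANCOVA) after four weeks (T3) and six months (T4), controlling for the baseline performance".

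Two other sections matter. Study design states: "The study consists of one intervention group (IG) and one waiting list control group". Main study outcomes states: "The effect of the program will be compared between the intervention group and the control group as well as between the different countries".

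**The concern.** The effect-size sentence gives a purpose and a calculation that do not fit each other. The purpose is a difference between two arms. The calculation yields one number per arm.

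A number computed inside one arm contains everything that happened to that arm between two measurements: the natural course after rehabilitation, regression to the mean, the effect of answering the questionnaire again, and other aftercare. The article itself gives reasons to expect such background change. The Background says that many patients find healthy behaviours hard to maintain after rehabilitation. It also says that German patients are offered aftercare that is not provided in the Netherlands. Per-arm effect sizes would carry these influences, possibly to a different degree in each country.

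The effect size is what a reader takes away as the size of the benefit. If the per-arm figure for the intervention group is read that way, the benefit can be overstated or understated even though the accompanying test is sound. It also could not be set beside the planning value ("The calculation was based on an effect size of 0.3, with a power (1-β) of 0.8 and alpha of 0.05") if that value is a between-arm difference. That would be usual for a two-group calculation, but the article does not say so.

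**Working it through.** The plan gives no figure to reproduce, so the check is one of wording, followed by a simple illustration.

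**Step 1. What can a per-arm effect size be?** Study design gives two arms. A contrast of intervention with control uses both arms and gives one number, so it cannot be computed separately in each. What remains is a measure inside one arm, and the natural one is change from baseline:

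- intervention arm: d_I = (mean post − mean pre) / SD = b + e
- control arm: d_C = (mean post − mean pre) / SD = b

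Here b is the background change common to both arms, e is the programme effect, and the SD is taken as common to both arms.

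**Step 2. What does it estimate?** The between-arm effect is e = d_I − d_C. The intervention arm's own figure equals e only when b = 0.

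**Step 3. Numbers.** All changes are assumed, in SD units. None comes from the article.

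| Control change | Intervention change (the per-arm figure) | True between-arm effect |
|---|---|---|
| 0.2 | 0.5 | 0.5 − 0.2 = 0.3 |
| 0.3 | 0.3 | 0.3 − 0.3 = 0 |
| −0.3 | 0 | 0 − (−0.3) = 0.3 |
| 0 | 0.3 | 0.3 − 0 = 0.3 |

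The per-arm figure overstates the effect in the first row. In the second it shows a benefit where there is none. In the third, where the programme prevents relapse, it hides a real one. It is right only in the last row, where the control arm does not change.

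**Step 4. Are the planned tests touched?** No. The regression and the ANCOVA compare the arms directly, so b cancels. In a simulation with 263 × 2 = 526 per arm (SD 1 and pre-post correlation 0.5, both assumed), both arms were given a change of 0.3 SD. Both within-arm changes were significant in 100% of runs, while the baseline-adjusted between-arm test rejected in 4.9%, close to its nominal 5%.

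**Step 5. The companion sentence.** Read literally, it compares the control group's pre-test and post-test values partly with the control group's own values. The preceding sentence names the intervention-versus-control comparison, so the intent can be recovered. This is a drafting slip.

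**The case against.** Four arguments deserve an answer.

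*The randomised comparison is already planned.* This stands. A reader might infer from the effect-size sentence that the trial would not report a between-arm result. The article does not support that: the regression, the baseline-adjusted ANCOVA and the statement of the main outcomes are all between-arm. The criticism must stay with the effect-size measure.

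*No false-positive problem is shown.* This also stands. A reader might infer that a difference will be declared when one arm's change is significant and the other's is not, with an inflated error rate. The plan writes no within-arm significance test and no such rule. Nor would one rate describe it. Take 526 per arm ("263 people have to participate in every group in each country", two countries), an assumed correlation of 0.5, SE = √(2 × 0.5 / 526) = 0.0436 and p = Φ(change/SE − 1.96). The chance 2p(1 − p) that exactly one arm is significant when there is no effect is then about 47%, 13% and 1% for assumed common changes of 0.10, 0.15 and 0.20 SD. The rate depends entirely on an unknown change, so no such figure belongs in the point.

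*The measure is undefined and its reference is not at hand.* This stands in part. Within-arm change is an inference and is labelled as one here. But with two arms, no reading of a separate per-arm effect size makes it the between-arm contrast.

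*A reader can subtract one per-arm figure from the other.* With a common SD, 0.5 − 0.2 does return 0.3. But the plan does not say that this will be done or that both arms share one SD. The subtraction would also not be baseline-adjusted like the ANCOVA, and it would come without a confidence interval.

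**Conclusion.** The point holds in a limited form. The effect size described cannot serve the purpose given for it, because a per-arm figure is not the difference between arms. Its error equals the background change: 0.2 SD in the main illustration (0.5 shown for a true 0.3), and it can go in either direction. That size rests on assumed changes. The mismatch itself rests only on the wording and on the trial having two arms. The reading as change from baseline is the likely one but is not stated.

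The planned between-arm tests are untouched, so the weight is modest: a sentence that should be corrected, not a flaw in the trial's main comparison. The companion sentence adds little beyond an editorial correction. Whether T3 and T4 are the best time points, given when the waiting list group gains access, is a separate question and is not decided here.

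**What to change.** Replace the effect-size sentence with:

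> The effect size is the baseline-adjusted between-group mean difference from the ANCOVA divided by the pooled baseline SD, with its 95% confidence interval, for each target behaviour and time point.

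If within-group effect sizes are kept, label them descriptive and state that they are not used to judge the difference between arms. Correct the companion sentence so that it compares the intervention group with the control group at post-test, adjusted for pre-test.

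The cost is two sentences. No new data are needed and no planned test changes, because the proposed effect size comes from the ANCOVA already specified.

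### The effect-size sentence seeks a difference between arms but computes a figure within each arm, which conflicts with the between-arm analyses planned in the same section

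*Protocol article*

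**What the plan says.** All references are to the protocol article.

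- **Study design** sets up two arms: "The study consists of one intervention group (IG) and one waiting list control group".
- **Main study outcomes** names the quantity of interest as a contrast: "The effect of the program will be compared between the intervention group and the control group as well as between the different countries".
- **Statistical analysis** plans two between-arm analyses. One is a test of "significant differences between the intervention group in comparison with the control group according to physical activity and nutrition by means of linear regression analysis". The other, given the task of assessing the programme's impact, reads "we intend to perform several analyses of covariance (ANCOVA) after four weeks (T3) and six months (T4), controlling for the baseline performance".
- **Statistical analysis** then adds: "In order to detect differences between the study condition and the control group, effect sizes will be calculated for each study group separately". A source is cited for this sentence, but no formula and no standardising SD are given.
- **Power analysis** uses a standardised effect: "The calculation was based on an effect size of 0.3, with a power (1-β) of 0.8 and alpha of 0.05".

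**The concern.** The effect-size sentence has a purpose and a method that do not match. Its purpose is to detect how the two arms differ. A figure worked out inside one arm cannot show that, because one arm has nothing to be compared with except its own baseline.

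A change from baseline contains everything that happens to participants after rehabilitation: natural course, regression to the mean, the effect of being measured again, and any programme effect. Randomisation separates the last from the others only when the arms are contrasted.

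This matters here because the Discussion section expects decline without support: "many patients fail to maintain lifestyle changes". A programme that works by preventing decline would show little or no change in its own arm. Its benefit would appear only as a gap to a falling control arm. Read singly, the per-arm figures could hide such a benefit, or credit the programme with a change that both arms share.

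**Working it through.** The plan gives no figure for this point, so there is none to reproduce. The check has four steps.

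**Inputs.** From the article: two arms, 263 participants per group per country (so 2 × 263 = 526 per arm over both countries), and a planning effect of 0.3. Assumed, because the article does not give it: a correlation r between baseline and follow-up of 0.5, with a range of 0.3 to 0.7 where it matters. Outcomes are scaled to SD 1.

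**1. What the separate figures contain.** Let the standardised change be c in the control arm and c + δ in the intervention arm, where δ is the programme effect. The separate figures are c and c + δ. Only their difference is δ.

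| Control change | Intervention change | Separate figures | Programme effect δ |
|---|---|---|---|
| 0 | 0.3 | 0 and 0.3 | 0.3 |
| -0.3 | 0 | -0.3 and 0 | 0 - (-0.3) = 0.3 |
| 0.3 | 0.3 | 0.3 and 0.3 | 0 |

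The intervention arm's own figure is 0.3, 0 and 0.3, while the programme effect is 0.3, 0.3 and 0. The own-arm figure does not track the effect.

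**2. What the planned ANCOVA gives.** A simulation with 263 per arm, r = 0.5 and 2,000 runs per case gave:
- Rows 1 and 2: mean adjusted difference 0.30 in both, with the null rejected in about 98% of runs.
- Equal changes of 0.10, 0.15 and 0.30 in both arms: mean adjusted difference within 0.004 of zero, with rejection in 3.85%, 5.35% and 5.90% of runs.

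The analysis already planned therefore recovers the contrast.

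**3. Scale.** A per-arm change can be divided by the baseline SD or by the SD of the change. The latter is √(2(1 - r)), so a change of 0.3 baseline SD becomes 0.3 / √(2(1 - r)):
- r = 0.3: 0.3 / √1.4 = 0.25
- r = 0.5: 0.3 / √1.0 = 0.30
- r = 0.7: 0.3 / √0.6 = 0.39

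The article does not say which SD applies. A per-arm figure may therefore differ in scale from the planning value of 0.3, but need not.

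**4. A worst case, for illustration only.** Suppose each arm's change were also tested at two-sided 0.05 and the verdicts compared. The article does not state this. With no programme effect, z = change / √(2(1 - r)/n). If p is the chance that one arm is significant, exactly one arm is significant with probability 2p(1 - p). With n = 526 and r = 0.5:
- change 0: p = 0.05, giving 2 × 0.05 × 0.95 = 9.5%
- change 0.085: z = 0.085 / 0.0436 = 1.95, p = 0.496, giving 50%
- change 0.2: z = 4.59, p about 0.996, giving about 1%

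The 50% is the maximum that 2p(1 - p) can reach, so it is not a typical value. With 263 per arm, the simulation gave 46% and 44% at changes of 0.10 and 0.15, and 0.3% at 0.30.

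**The case against.** The strongest reply is that the programme effect is already analysed properly. The regression and the baseline-adjusted ANCOVA stand in the same section, and the ANCOVA is the analysis assigned to the programme's impact. This is right, and it confines the point to effect-size reporting. It does not repair the sentence, which still assigns the detection of arm differences to per-arm figures and does not say how these relate to the ANCOVA.

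A second reply is that the article never says the figures are pre-post changes. This also stands. The formula may lie in the cited source or the full analysis plan, and the Randomization section uses the term study group for the intervention arm alone, so the sentence could mean each study group against control. That reading fits poorly, since with a single intervention arm the words for each and for separately have nothing to do. If it is what was meant, the sentence still needs rewording.

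A third reply is that per-arm standardised changes can be subtracted. With a common SD this gives the unadjusted difference in change, as in row 2 of the table. That is true, but the article does not state the subtraction.

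Two stronger readings are tempting. A reader might infer that these figures are the trial's headline result, but no section makes them primary or the criterion of effectiveness. A reader might also infer a 50% risk of a false impression. That needs a significance verdict in each arm, which the sentence does not mention, and a change chosen to give the maximum.

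**Conclusion.** The point holds as a conflict confined to one sentence. The stated aim is a between-arm difference, the stated method is a figure per arm, and the two do not fit each other or the contrast named under Main study outcomes.

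The possible size of the mismatch is the whole programme effect: in the example with declining controls, the intervention arm's own figure is 0 where the effect is 0.3. The example rests on reading the figures as within-arm changes, which is the natural reading but is not stated, and on an assumed decline of 0.3 SD in controls.

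The planned regression and ANCOVA are unaffected, and the documents do not support a claim that the trial relies on within-arm comparisons. The correction is worth making because the effect size is the figure that readers would naturally set beside the planning value of 0.3.

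**What to change.** Replace the sentence with wording such as: For each behaviour and each analysed time point, one between-arm standardised effect will be reported, namely the baseline-adjusted mean difference (intervention minus control) from the ANCOVA divided by the T1 SD pooled over both arms, with its 95% confidence interval. Changes within each arm may be tabulated as description and will not be used to judge effectiveness.

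The cost is one sentence. The planned ANCOVA supplies the numerator and the T1 data supply the SD. No added measurement, model or participant is needed, and no figure in the article changes.
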